#### Ensuring participant retention

Given that this is a 12-month trial, baseline and follow-up data will be collected in separate school years (summer holidays in-between). This implies that there might be some losses to follow-up as children might change residence/school. We have increased the trial size accordingly to compensate for 11% attrition (i.e. derived from the proportion of children continuing in the same school the following year). Fieldwork teams will stay in schools for an entire week (as they progress screening children from one classroom to another) to give an option to those children who were absent the day that their classroom was screened. That aside, we expect a high completion rate as parental consent will be sought for both waves of data collection simultaneously. Using a clinical outcome measure will prevent further losses to follow-up as schools are captive populations. Attrition could be higher for parental questionnaires (used to estimate child dental visits). However, we are also collecting information on dental visits from the children’s perspective. Furthermore, dental visits are the secondary outcome and will not affect the main conclusion of the trial.

#### Data storage and management

The principal investigator will be responsible for all data entry and management. Personal identifiable information will be collected to regain contact with participants for the follow-up assessment and link baseline with follow-up data. This will be handled through pseudo-anonymisation, whereby the principal investigator will keep a separate file containing personal identifiable information for all participants and assign an artificial identifier (code) to each as they enter the study. Everybody else involved in the study will work with coded data when collecting or analysing information.

Data entry will be done using codes and no personal information will be kept electronically. Coded data will be entered to a password-protected device (laptop) owned by the primary researcher on an ongoing basis as data collection progresses. Once data collection has been completed, all paper forms (consents, questionnaires and clinical examination) will be transferred to a locked cabinet and electronic files transferred to a password-protected desktop computer both located at King’s College London Dental Institute. No data will be accessed by anyone other than the three members of the research team.

### Data analysis

#### Justification of sample size

Based on a previous relevant study [15], a sample size of 910 children (455 in each trial group) is required to detect a 0.50-unit difference in the number of teeth with untreated caries between the conventional screening group and specific screening group, assuming 80% statistical power, 5% significance level and intra-class correlation coefficient (ICC) for dental caries at school level of 0.03. The total sample size will be rounded up to 1010 (505 in each group) to allow for a dropout rate of up to 11%. After compensating for the clustering of children within schools, there will be six clusters per group, each cluster will include at least 75 participants.

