### Trial design

This will be a cluster randomised, assessor-blinded, superiority trial with two groups running in parallel and an allocation ratio of 1:1. The trial will be conducted over 12 months, from baseline to follow-up outcome assessments. Randomisation at cluster level (school) will prevent contamination that could arise from delivering both interventions in the same school (i.e. randomisation at child level) while also accounting for variations between schools and areas in which the schools are located.

The trial is sponsored by King’s College London. It is a PhD project carried out by the principal investigator (HA) and supervised by WS and EB. The progress of the study will be closely monitored by a PhD Committee (acting as a Trial Steering Committee), including the principal investigator, the two supervisors and two independent external examiners.

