### Setting and participants

The trial will be conducted across 16 primary schools in Riyadh city, Saudi Arabia. A list of all governmental primary schools in Riyadh city, Saudi Arabia, will be obtained from the Ministry of Education and stratified according to area (schools located in high-socioeconomic and low-socioeconomic areas). Schools with in-house dental clinics and participating in any dental screening/preventive programme will be excluded from the trial.

Children in selected primary schools will be considered eligible to join the trial if they meet all inclusion criteria and none of the exclusion criteria.

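### The enrolment target of 1010 does not cover the stated 11% dropout: it covers about 9.9%, and 11% loss leaves about 899 children against the 910 required

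*Protocol article*

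**What the plan says.** The protocol article (Justification of sample size) states that "a sample size of 910 children (455 in each trial group) is required to detect a 0.50-unit difference"; the outcome is the count of untreated decayed teeth. It gives its assumptions in these words: "assuming 80% statistical power, 5% significance level and intra-class correlation coefficient (ICC) for dental caries at school level of 0.03". The next sentence sets the enrolment target: "The total sample size will be rounded up to 1010 (505 in each group) to allow for a dropout rate of up to 11" per cent.

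The section on ensuring participant retention makes the same claim: "We have increased the trial size accordingly to compensate for 11% attrition". It adds that the rate was derived from the proportion of children who continue in the same school the following year. The 11% is therefore a share of enrolled children who are lost, and the retained share is 0.89.

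The inflation formula is not written out in either place.

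**The concern.** The article states three numbers that are tied by simple arithmetic: the number required at the end (910), the number to be enrolled (1010) and the loss between the two (up to 11%). Any two of them fix the third, and the stated three do not agree. The wording makes 11% the limit that the target should withstand, and the retention section gives it as the loss to be expected when children change residence or school between school years. At that loss the trial would finish with fewer children than the article itself calls required, while stating in two places that the loss has been covered.

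What is at stake is the accuracy of a stated design figure. The effect on power is small and is sized below.

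**Working it through.** **Inputs**, all from the protocol article: required number 910, 455 per group (Justification of sample size); target 1010, 505 per group (same section); loss 11% of those enrolled (Justification of sample size; meaning from Ensuring participant retention); 1:1 allocation (Trial design); ICC 0.03 and difference 0.50 (Justification of sample size).

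**1. How the stated target arises.** Multiplying the requirement by one plus the dropout rate gives

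- 910 × 1.11 = 1010.1
- 455 × 1.11 = 505.05

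Both stated figures, 1010 and 505, are recovered. Equivalently, the 100 added children are 100/910 = 11.0% of the requirement. The article shows no formula, so this is an inference from the match. The remaining steps do not depend on it.

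**2. What remains at 11% loss.** Retained = enrolled × (1 − loss):

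- 1010 × 0.89 = 898.9, about 899
- 505 × 0.89 = 449.45 per group, that is 449 to 450
- Shortfall: 910 − 898.9 = 11.1, about 11 children, or 11.1/910 = 1.2%

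**3. What loss 1010 does cover.** 1 − 910/1010 = 100/1010 = 9.9%.

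**4. What keeping 910 at 11% loss takes.** Enrolled = required/(1 − loss):

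- 910/0.89 = 1022.5, rounded up to 1023
- 455/0.89 = 511.2, rounded up to 512 per group, 1024 in total

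That is 13 to 14 more than 1010.

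**5. Effect on power.** The article gives no SD, so this step rests on assumptions: a two-sided 5% test and a normal reference distribution.

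*(a) Upper figure, design effect held constant.* If 455 per group gives exactly 80%, the standardised difference is 1.960 + 0.842 = 2.802. With 449.45 per group it becomes 2.802 × √(449.45/455) = 2.784. Power = Φ(2.784 − 1.960) = 79.5%, a loss of about 0.5 points. The SD cancels here.

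*(b) Lower figure, schools fixed.* Children leave but schools do not, so school size and the design effect both fall. Take six schools per group, as in the sample-size paragraph, ICC 0.03 and an assumed SD of 1.5. That SD is close to the value that makes 455 per group in six schools yield 80%.

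| Per group | Children per school | Design effect = 1 + (m − 1) × 0.03 | SE = 1.5 × √(2 × design effect/n) | Power = Φ(0.50/SE − 1.960) |
|---|---|---|---|---|
| 455 | 75.8 | 3.245 | 0.1791 | 79.7% |
| 449.45 | 74.9 | 3.217 | 0.1795 | 79.6% |

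The unrounded loss is about 0.14 points. The two approaches bracket the cost at roughly 0.1 to 0.5 points.

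**The case against.** *The gap is trivial.* It is 11 analysed children out of 910, and 1010 lies within 1.3% of 1023 (13/1010). No analysis or conclusion turns on it. That stands, and it limits how much weight the point can bear. It does not make the sentence correct.

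*The 11% may have been meant as a mark-up on 910.* The arithmetic fits that reading, since 100/910 = 11.0%. But the article calls the figure a dropout rate and an attrition rate, and derives it from the share of children who stay in their school. A rate of that kind applies to those enrolled.

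*The larger number of schools makes up the loss.* The sample-size paragraph says "there will be six clusters per group, each cluster will include at least 75 participants", whereas the setting section says "The trial will be conducted across 16 primary schools in Riyadh city, Saudi Arabia". With eight schools per group, 449.45 children per group and the same assumptions as in step 5(b), power would be about 87%. So a reader might infer from the shortfall that the trial will be underpowered, and the documents do not support that. The mismatch between 12 and 16 schools is a separate matter. It leaves the dropout sentence as it is, because that paragraph still calls 910 the required number.

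*The cause is not shown.* A reader might take it as established that the authors multiplied by 1.11 where they should have divided by 0.89. The near-exact match makes this likely, but the article gives no formula and says only that the number was rounded up. The shortfall is the finding; its cause is an inference.

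**Conclusion.** The point holds as an arithmetic inconsistency in a stated design figure. With the required number, the target and the loss as the article gives them, 1010 covers about 9.9% dropout and not 11%. At 11% about 899 children remain, 11 fewer than required. This rests only on the article's own numbers and on reading the 11% as a loss out of those enrolled, which the retention section supports.

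The consequence is minor. The power cost of roughly 0.1 to 0.5 points varies with the method, and the lower end also depends on an assumed SD of 1.5. No absolute power figure can be attributed to the plan, because it states neither an SD nor a reference distribution. The 910 itself cannot be reproduced for the same reason, and it is taken here as given.

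**What to change.** In the justification of sample size, replace the dropout clause with one of two true statements:

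- 1010 children (505 per group) allow for a dropout of about 9.9% from the required 910; or
- with 1010 enrolled and 11% dropout, about 899 children (449 to 450 per group) would be analysed.

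Then align the sentence in the retention section, so that it no longer says that 11% attrition is fully compensated. If the team prefers to keep both 910 analysed and 11% loss, the target to state is 1023, or 1024 with equal groups.

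Quote no power figure alongside the change unless the SD and the reference distribution behind it are given and labelled as assumptions.

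The cost is one sentence in one section and a matching edit in another. Either of the two restatements needs no extra children, which matters because the trial status section expects recruitment to be completed by April 2018. Only the third option adds children, 13 or 14 of them.

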**Methods:**

This is a cluster randomised controlled trial comparing referral of screened-positive children to a specific treatment facility (King Saud University Dental College) against conventional referral (information letter advising parents to take their child to a dentist). A thousand and ten children in 16 schools in Riyadh, Saudi Arabia, will be recruited for the trial. Schools (clusters) will be randomly selected and allocated to either group. Clinical assessment for dental caries will be conducted at baseline and after 12 months by dentists using the World Health Organisation (WHO) criteria. Data on sociodemographic, behavioural factors and children’s dental visits will be collected through structured questionnaires at baseline and follow-up. The primary outcome is the change in number of teeth with untreated dental caries 12 months after referral. Secondary outcomes are the changes in the proportions of children having untreated caries and of those who visited the dentist over the trial period.

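### The sample-size section describes 12 schools of at least 75 children, but the trial is stated to run in 16 schools of about 63, and the power claim is not restated for that layout

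*Protocol article*

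**What the plan says.** The section Justification of sample size states that "a sample size of 910 children (455 in each trial group) is required to detect a 0.50-unit difference". That difference refers to the count of untreated carious teeth, and the size is worked out "assuming 80% statistical power, 5% significance level and intra-class correlation coefficient (ICC) for dental caries at school level of 0.03". The section raises the total to 1010 (505 per group) for dropout of up to 11%. It then says that, once clustering is allowed for, "there will be six clusters per group, each cluster will include at least 75 participants". Two groups of six is 12 schools.

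Setting and participants says otherwise: "The trial will be conducted across 16 primary schools in Riyadh city, Saudi Arabia". So does the Methods paragraph of the abstract: "A thousand and ten children in 16 schools in Riyadh, Saudi Arabia, will be recruited for the trial".

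Three other points bear on this. Trial design gives a 1:1 allocation ratio. Randomisation specifies simple randomisation of schools within area strata. The sample-size section refers to an earlier study for its basis but gives no SD for the outcome.

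**The concern.** In a cluster trial the number of schools and the number of children per school fix the design effect, the effective sample size and the degrees of freedom. The article gives two incompatible sets of these figures. The set in the sample-size section, which carries the power claim, is not the set given for the trial itself. A reader cannot tell which design the 80% belongs to, and cannot recompute it for 16 schools because the SD is missing. Trial status says recruitment was still open at protocol version 3, so the number of schools was still a live matter.

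**Working it through.** **Inputs from the article.** 455 evaluable per group (910 in total); 1010 recruited; difference 0.50 teeth; power 80%; significance level 5%; ICC 0.03; six schools per group with at least 75 children each (sample-size section); 16 schools (abstract, setting). **Assumed.** A two-sided test, a comparison of two means, and an even split of schools unless noted. The SD is not stated.

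**1. Counts**

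| Layout | Recruited per school | Evaluable per school |
|---|---|---|
| 12 schools | 1010/12 = 84.2 | 910/12 = 75.8 |
| 16 schools | 1010/16 = 63.1 | 910/16 = 56.9 |

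Only 12 schools agrees with at least 75 per school. With 16 schools, 75 each would need 16 × 75 = 1200 children, against 1010 planned.

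**2. Reproducing 455 per group**

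Design effect = 1 + (m − 1) × ICC. At m = 75 this is 1 + 74 × 0.03 = 3.22.

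The size before clustering is 455/3.22 = 141.3 per group. From n = 2 × ((1.96 + 0.8416) × SD/0.50)², the SD is 0.50 × √(141.3/2)/2.8016 = 1.50.

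Forwards at SD 1.5: n = 141.28; 141.28 × 3.22 = 454.9, which rounds to 455; 454.9/75 = 6.07 schools. So 455, 75 and six fit one another at a round SD.

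The solution is not unique. With 56.9 evaluable per school (design effect 2.68), 455 follows from an SD of 1.65. With 63.1 per school (2.86), it follows from 1.59.

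**3. Power at SD 1.5**

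Effective n per group = 455/design effect; SE = SD × √(2/effective n).

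- 12 schools: design effect 1 + 74.83 × 0.03 = 3.245; effective n 140.2; SE 0.179; 0.50/SE = 2.79. Power is 79.7% (normal) or 71.1% (t, 10 df).
- 16 schools: design effect 1 + 55.875 × 0.03 = 2.676; effective n 170.0; SE 0.163; 0.50/SE = 3.07. Power is 86.7% (normal) or 81.5% (t, 14 df).

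If a full 11% of 1010 is lost, 1010 × 0.89 = 899 remain, or 56.2 per school. The 16-school figures are then 86.6% and 81.4%.

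**4. Range over the unstated SD** (910 evaluable, even split)

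| SD | 12 schools, normal / t | 16 schools, normal / t |
|---|---|---|
| 1.4 | 84.9% / 76.9% | 90.9% / 86.4% |
| 1.5 | 79.7% / 71.1% | 86.7% / 81.5% |
| 1.6 | 74.4% / 65.6% | 82.2% / 76.4% |
| 1.7 | 69.2% / 60.4% | 77.4% / 71.3% |
| 2.0 | 55.3% / 47.3% | 63.5% / 57.4% |

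The level depends on the SD. The direction does not, because the effective n is 170 against 140 at any SD.

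**5. Uneven split of 16 schools** (SD 1.5, normal approximation): 86.7% at 8:8, 86.2% at 7:9, 84.5% at 6:10, 81.3% at 5:11 and 75.9% at 4:12.

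**The case against.** The strongest reply is that no harm to the trial is shown. A reader might infer from the mismatch that the trial is underpowered. The documents do not support that: the same children spread over more schools give more power, and at SD 1.5 the 16-school layout exceeds 80% on either reference when the split is even. This part of the reply stands.

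Other strong readings also fail:

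- **That 455 can arise only from 75 per school and an SD of 1.50.** Step 2 shows other pairs that give it. It remains possible that 455 was worked out for 16 schools and that only the closing sentence is out of date. The 12-school origin is the likelier reading, because 75.8 matches the stated minimum, but it is an inference.
- **That six schools of 75 fall short of 455, or that 12 schools miss 80%.** The article says at least 75, and 75.8 satisfies that. A power of 79.7% is 80% after rounding.
- **That the 71% for 12 schools exposes an error in the protocol.** The article does not say which quantiles were used. The SD of 1.5 was back-solved with normal quantiles. Had a t reference on 10 df been used in planning, the implied SD would be 1.35, power with 12 schools would be 80% by construction, and 16 schools would give about 89%.
- **That the fieldwork would stop at 12 schools.** The abstract and the setting section both say 16.

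The missing SD may well be in the full protocol or the cited study, so its absence is no separate fault. None of this removes the contradiction. The article does not call six a minimum and does not present four schools as reserves. Data collection says that refusing schools are replaced from the list, so the extra four are not explained as cover for refusals.

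**Conclusion.** The article is wrong as written. Twelve schools and 16 schools cannot both be the design, and 16 schools, at least 75 children per school and 1010 children cannot all be true. The stated 80% power most likely belongs to the 12-school layout. For the 16 schools named elsewhere, the article gives no matching cluster size or power.

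This is a fault of consistency and reporting in figures that the power claim relies on. The gain from 12 to 16 schools is about 7 percentage points by normal approximation (80% to 87%) and about 10 on a t reference (71% to 81.5%). These levels hold only for SD 1.5, ICC 0.03, a two-sided 5% test and an even split. That 16 schools give more power than 12 does not depend on the SD.

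**What to change.** Reconcile the abstract, Setting and participants, and Justification of sample size on the number and size of schools.

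If 16 schools stands, replace the closing sentence of the sample-size section with the layout to be run: 16 schools, about 63 children recruited and 57 evaluable per school, and a design effect of about 2.7 at an ICC of 0.03. Then restate the power, or the detectable difference, for that layout:

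- Use the authors' own planning SD for the 12-month outcome, and state it. The 1.5 used here is inferred and should not be copied in as a planning assumption. Nor will the SD of the baseline counts serve as it stands, since the primary outcome is the change over 12 months.
- Use a small-sample (t) reference, because only 16 schools supply the degrees of freedom.
- Note that simple randomisation within strata may not give exactly eight schools per group, and say what a less even split would do.

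If 12 schools is the design, correct the abstract and the setting section instead.

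The cost is wording and one recalculation. No school or child is added if 16 stands. The restated power may differ from 80% in either direction, depending on the SD.

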#### Between-group comparisons

A comparison of demographic (sex, age), socioeconomic (family income, parental education) and behavioural characteristics (tooth-brushing frequency, dental attendance pattern, last dental visit, reason for last dental visit, use of fluoridated toothpaste and sugars intake) and caries levels in deciduous and permanent teeth between both intervention groups will be carried out using the chi-square test for categorical variables and a *t* test for continuous variables.

We will report absolute and relative measures of effect; that is, absolute and relative difference in means for continuous outcomes (change in number of teeth with untreated caries) and risk differences and relative risks for dichotomous outcomes (changes in the proportions of children having teeth with untreated caries and visiting the dentist). For the primary outcome (change in number of teeth with untreated caries), negative binomial regression will be used to estimate relative differences (incidence rate ratios) and predictive margins to estimate absolute differences between intervention groups. This analytical technique will allow accounting for stratification of the sample, clustering of children within schools and any baseline socioeconomic and behavioural differences between trial groups. For secondary outcomes, log-binomial regression will be used to estimate relative risks for the change in the proportions of children with untreated dental caries and who visited the dentist. Predictive margins will also be used to estimate absolute differences in each secondary outcome. Intention-to-treat analysis will be used to handle missing values in categorical outcomes. Multiple imputation will be considered as an option for continuous outcomes.

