The selected study design addresses some of the methodological limitations of previous studies [7, 8]. Data collection on participants’ socioeconomic and behavioural factors will help accounting for baseline differences between the two trial groups (if they are unbalanced after randomisation) that might impact use of dental services [21]. However, this study must be conducted with relatively limited resources as part of PhD project and will probably not answer all relevant questions on the effectiveness of school dental screening in Saudi Arabia. Future research should build upon what we are starting in this study, by looking into cost-effectiveness analysis and reasons behind any lack of effectiveness. A national study could also provide more information on effectiveness in different parts of the country.

Finally, it is worth noting that the education system in Saudi Arabia is segregated by children’s gender. Due to cultural restrictions, female dentists cannot access boys-only schools and vice versa. Although we have recruited and trained separate teams for accessing boys- and girls-only schools, access to both types of schools are heavily dependent on approval from the Ministry of Health as the principal investigator, who will oversee the entire fieldwork, is female. This might result in a male-to-female ratio different to 1-to-1.

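### Baseline comparisons use chi-square and t tests that ignore school clustering, and adjustment of the primary model depends on observed imbalance instead of a covariate set fixed in advance

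*Protocol article*

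**What the plan says.** All places are in the Protocol article.

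- **Trial design.** The school is the randomised unit: "Randomisation at cluster level (school) will prevent contamination".
- **Between-group comparisons, first paragraph.** The arms are compared at baseline on 12 items: sex and age; family income and parental education; six behavioural items; and caries in deciduous and in permanent teeth. The comparison "will be carried out using the chi-square test for categorical variables", with a t test for continuous variables.
- **Between-group comparisons, second paragraph.** Clustering is mentioned only for the outcome regression. The negative binomial model for the primary outcome is to account for stratification, "clustering of children within schools and any baseline socioeconomic and behavioural differences between trial groups".
- **Discussion.** Baseline data are to help account for differences between the arms "if they are unbalanced after randomisation". The same section says that schools are segregated by gender.
- **Justification of sample size.** The calculation assumes an "intra-class correlation coefficient (ICC) for dental caries at school level of 0.03".

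No covariate is named for the primary model apart from the stratification and clustering terms.

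**The concern.** Ordinary chi-square and t tests treat children as independent. Here whole schools were allocated, and the protocol itself expects children in one school to resemble each other. The tests therefore understate chance variation between arms and report differences as significant too often.

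Sex is the plainest case. It is constant within a single-gender school, so a child-level chi-square treats 12 to 16 units as if they were about 1010.

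Two things are at stake. The baseline table would carry misleading p-values. In addition, adjustment of the primary model depends on which socioeconomic and behavioural differences happen to appear, so the model is not known until the data are seen. Even a valid baseline test would be a poor guide, because under randomisation it measures chance and not prognostic importance. The rule as worded also does not reach baseline caries or age, which are plausible predictors of untreated caries at 12 months.

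**Working it through.** **Inputs from the protocol**
- ICC 0.03, given for caries at school level (Justification of sample size).
- 1010 children in 16 schools (Abstract; Setting and participants): 1010 / 16 = 63.1 per school.
- In the sample-size section, by contrast, "there will be six clusters per group, each cluster will include at least 75 participants", that is 12 schools of 75. The two statements disagree, so both are carried through.
- 5% significance level; two-sided is assumed because the sidedness is not stated.

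**The protocol's own figures**
- 910 × 1.11 = 1010.1, which matches the stated 1010. Dividing by 0.89 would give 1023, so the figure agrees to within about 1%.
- The 455 per arm cannot be rebuilt independently, because no SD is given. It is compatible with a design effect for schools of 75: 1 + 74 × 0.03 = 3.22, and 141.3 × 3.22 = 455, where 141.3 per arm corresponds to a difference of 0.50 with a back-solved SD of 1.50. So the sample size can be explained by an allowance for clustering that the baseline tests do not make.

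**Step 1: design effect, DE = 1 + (m − 1) × ICC**
- 16 schools: 1 + 62.1 × 0.03 = 2.86
- 12 schools: 1 + 74 × 0.03 = 3.22

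**Step 2: true rejection rate of an unclustered 5% test when only chance is at work, 2 × [1 − Φ(1.96 / √DE)]**

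| Layout | ICC 0.01 (assumed) | ICC 0.03 | ICC 0.10 (assumed) |
|---|---|---|---|
| 16 schools of about 63 | 12.4% | 24.7% | 46.6% |
| 12 schools of 75 | 13.7% | 27.5% | 49.9% |

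A simulation with 5,000 replicates per setting, without strata, gave 24.3% and 27.2% at ICC 0.03. A t test on school means in the same data rejected 4.9% and 4.6% of the time.

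**Step 3: variables that the adjustment wording can admit**

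Of the 12 tested items, only the socioeconomic (2) and behavioural (6) ones fall under it, which makes 8.
- Expected chance flags: 8 × 0.247 = 2.0, or 8 × 0.275 = 2.2. At a true 5%: 8 × 0.05 = 0.4.
- Chance of at least one flag, if the variables are independent: 1 − (1 − 0.247)^8 = 90%, or 1 − (1 − 0.275)^8 = 92%. At a true 5%: 1 − 0.95^8 = 34%.

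**Step 4: sex**

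With ICC about 1 the design effect equals the school size, and the same formula gives about 80% to 82%. With so few schools the normal approximation is rough, so this is indicative only.

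**The case against.** **No selection rule is written.** The protocol never says that a test result picks a covariate, and it gives no threshold. A reader might infer that covariates enter by p-value; the text does not say so. What it does say is that adjustment is for differences between arms, if present, and the only method it describes for finding them is these tests. The dependence on observed imbalance is stated; the p-value mechanism is inferred.

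**Scope.** A reader might count about 3 chance flags among all 12 variables (12 × 0.247) and suppose that all of them reach the model. Sex, age and caries lie outside the adjustment wording, so the relevant count is about 2 of 8. The misleading test on sex affects the baseline table only.

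**The ICC.** The 0.03 is given for caries. Applying it to income, education or behaviour is an assumption. Stratifying by area may reduce between-arm variation in income and education, and no within-stratum figure is given. This objection stands, which is why a range is shown. The rate exceeds 5% throughout it.

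**The primary result.** A reader might infer that the primary p-value or confidence interval is wrong. The outcome model is said to account for clustering, and every figure above concerns baseline tests. No inflation of type I error or bias in the treatment effect has been shown. Nor is adjusting for a real chance difference in a prognostic factor harmful in itself.

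**Baseline caries.** The outcome is a change, so the baseline count already enters it. That is true, but a change score does not condition on baseline. Any loss of precision has not been quantified.

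**An unseen analysis plan may list the covariates.** It may, and a missing list alone would not be a finding. The article, however, states unclustered tests and a conditional adjustment rule, and those are what is criticised.

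**Conclusion.** The point holds in limited form. The stated baseline tests are invalid for a school-randomised trial. At ICC 0.03 they reject by chance about 25% of the time with 16 schools and about 27% with 12, roughly five times the nominal rate. Over an assumed ICC range of 0.01 to 0.10 the rate runs from about 12% to 50%. Adjustment of the primary model is tied to observed imbalance in socioeconomic and behavioural variables. If the tests are what identifies imbalance, about 2 of 8 would be flagged by chance.

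These figures assume that the tests are applied to individual children (inferred from their plain names), equal school sizes and arms, the caries ICC for the other variables, and independence between variables for the chance of at least one flag. The defect is confined to the baseline p-values and to covariates left to the data. It should be corrected, but it is not evidence that the treatment-effect standard error is wrong.

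**What to change.** 1. Replace the baseline tests with a descriptive table by arm (means or percentages). If tests are kept, use versions that allow for clustering by school.
2. Fix the primary-model covariates in advance on prognostic grounds: the area stratum (the model is already meant to reflect stratification), the baseline untreated-caries count, and age or grade. Keep any further covariates few, because there are only 12 to 16 schools; school-level covariates such as school gender are the most costly in that respect.
3. Remove the wording that makes adjustment in the primary model conditional on imbalance. Report adjustment for other observed imbalances only as a sensitivity analysis.

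The cost is a change of wording. The variables are already being collected, the sample size is unaffected, and the change can be made before follow-up outcomes are analysed.
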